### Drug administration

Subjects will receive either 300,000 IU (7.5 mg) of vitamin D or placebo seven days prior to planned oesophagectomy. The drug will be administered by qualified medical or nursing staff.

### Concomitant medications

Patients taking the following medications are not eligible for inclusion in the study:

• Taking more than 1,000 IU/day (25 mcg/day) vitamin D supplementation by month preceding enrolment.

• Taking cardiac glycoside, carbamazepine, phenobarbital, phenytoin, primidone or long-term immunosuppressant therapy.

• Patients taking benzothiadiazine derivatives at doses higher than that which is recommended in the British National Formulary (BNF).

• Patients taking a benzothiadiazine derivative in combination with a calcium supplement.

### Post randomisation withdrawals and exclusions

Subjects may withdraw from the trial or the trial treatment at any time without prejudice. If a subject withdraws from the trial treatment, then they will be followed-up wherever possible and data collected as per protocol until the end of the trial. The only exception to this is where the subject also explicitly withdraws consent for follow-up.

### Blinding/un-blinding

Patients, clinical and research / trial staff will be unaware of the arm of the study to which a patient is allocated. Active and placebo treatment packs and their contents will be identical in appearance. The protocol allows for emergency un-blinding in the event of significant concerns about patient safety. In the unlikely event that un-blinding is required the local investigator will discuss this with the Chief Investigator. All events will be logged.

### Monitoring and reporting adverse events

VINDALOO is recruiting a population who are prone to recognized medical and surgical complications. It is expected that many of the patients will experience an event that might be seen as a serious adverse event but is a recognized complication following oesophagectomy. Adverse and serious adverse events which are recognised complications of surgery, for example, medical (pneumonia, sepsis) and surgical (chyle leak, anastamosis leak) will be recorded in the case report form.

Death and other serious adverse events thought to be related to the study drug or serious unexpected serious adverse reactions will be reported to the trial co-ordinating centre and Chief Investigator within 24 hours of becoming aware of their occurrence. The Chief Investigator will inform the sponsor and regulatory authorities.

### Data collection

Data up until hospital discharge will be recorded in each subject's Case Report Form (CRF) by a member of the trials team. Most of the data collected will be obtained from the patient’s hospital notes. In the unlikely event that a subject is transferred to another hospital, the study team will ensure that data collection is completed by the receiving hospital.

If the subject remains in hospital at 28 or 90 days, survival at these time points will be recorded by hospital staff. Mortality after hospital discharge will be obtained from the National Health Service (NHS) Statistical Tracing Service (NSTS).

### Statistical analysis plan

Data will be analysed with the help of the trial statistician. Data will be analysed using SPSS for Windows 17.0. A detailed analysis plan will be developed during the trial prior to commencement of analysis. In brief, for continuously distributed data, differences between groups will be tested using independent samples t-tests with transformations of variables to Normality if appropriate, or non-parametric equivalents. Chi-squared tests (or Fisher’s Exact tests) will be used for categorical variables. A *P* value of 0.05 will be considered as significant. We will test for significant correlations between changes in the biological markers using standard methods. The treatment effect will be analysed on an intention-to-treat basis. For further examinations of relationships between a binary variable and known explanatory variables, the following tests will be applied as appropriate. Logistic regression will be used to provide the estimated risk ratios for the treatment effect with associated 95% confidence interval (CI). Time to event outcomes, such as duration of ventilation or duration of hospital stay, will be analysed by survival methods and reported as hazard ratios and 95% CI. A single final analysis is planned at the end of the trial.

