**Methods/Design:**

The ‘Vitamin D to prevent lung injury following oesophagectomy trial’ is a multi-centre, randomised, double-blind, placebo-controlled trial. The aim of the trial is to determine in patients undergoing elective transthoracic oesophagectomy, if pre-treatment with a single oral dose of vitamin D_3_ (300,000 IU (7.5 mg) cholecalciferol in oily solution administered seven days pre-operatively) compared to placebo affects biomarkers of early acute lung injury and other clinical outcomes. The primary outcome will be change in extravascular lung water index measured by PiCCO® transpulmonary thermodilution catheter at the end of the oesophagectomy. The trial secondary outcomes are clinical markers indicative of lung injury: PaO_2_:FiO_2_ ratio, oxygenation index; development of acute lung injury to day 28; duration of ventilation and organ failure; survival; safety and tolerability of vitamin D supplementation; plasma indices of endothelial and alveolar epithelial function/injury, plasma inflammatory response and plasma vitamin D status. The study aims to recruit 80 patients from three UK centres.

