### Outcome measures

#### Primary outcome

The primary outcome will be the extravascular lung water index (EVLWI) measured by PiCCO thermodilution catheter at the end of the oesophagectomy (measured within one hour post-operatively). In ALI the changes in lung compliance that are a cardinal feature of this disease occur due to the accumulation of extravascular lung water (EVLW). The PiCCO EVLWI has been shown to be an independent risk factor for mortality in ALI and has been used as the primary outcome in several clinical trials in ALI (BALTI-1, HARP) [32,33] as well as post-thoracotomy [34]. In BALTI-1 we demonstrated that the transpulmonary thermodilution technique (PiCCO) is able to detect a significant change in lung water with a treatment that might be expected to achieve this objective. We have tested the CV coefficient of variance of EVLWI measurements previously and found it to be 6.8% over six sequential assessments over two hours. Further, we have studied the perioperative changes in lung water following oesophagectomy and demonstrated that preoperative vitamin D status influences the level of accumulation of EVLW.

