### Power and sample size estimate

There are no direct data to predict the effect size of vitamin D replacement upon EVLWI. In our preliminary work with 50 patients, the patients with 25(OH)D_3_ concentrations less than 15 nmol/L had the greatest increases in EVLWI (+3.2 ml/kg, +27%) compared to those patients with less severe deficiency pre–postoperatively (+1.0 ml/kg, +10% *P* = 0.013) suggesting that severe vitamin D deficiency influences EVLWI. As a group, after undergoing oesophagectomy our patients have a mean post-operative EVLWI of 10.1 ml/kg and standard deviation of 2.9 ml/kg. For the study to be able to detect a change of 20% in EVLWI with a power of 80% we will require approximately 34 patients in each arm to reach the primary endpoint (*P* = 0.05). An additional six patients will be needed to allow for dropouts, such as open/close cases, unexpected deaths and other difficulties with data collection. Thus, we intend to recruit 40 patients to each arm of the study.

With 34 patients completing each arm of the study, based upon preliminary unpublished data from 50 oesophagectomy cases, this study would detect a treatment effect of vitamin D upon the PO_2_:FiO_2_ ratio postoperative (PO) of ± 8.16 (± 20%), PO plasma soluble intercellular adhesion molecule-1 (sICAM-1) of ± 16 ng/ml (± 32%), plasma C-reactive protein (CRP) ± 53 ng/ml (± 33%), PO plasma von Willebrand factor (vWF) ± 55% relative to control plasma (± 24.7% change), PO plasma high-mobility group box 1 (HMGB-1) 5.42 ng/ml (± 54%), PO plasma myeloperoxidase (MPO) 105 pg/ml (± 57%), PO plasma MMP-9 51 ng/ml (± 57%), and PO plasma surfactant protein-D (SP-D) 691 ng/ml (± 61%). All calculations assume 80% power at a two-tailed significance level of 0.05.

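### The unadjusted t-test for EVLWI is valid but makes no use, or inefficient use, of the pre-operative value; baseline-adjusted ANCOVA would be at least as powerful under either definition of the primary outcome

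*Protocol article*

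**What the plan says.** The Statistical analysis plan section of the protocol article covers all continuous outcomes in one sentence: "differences between groups will be tested using independent samples t-tests", with transformation where appropriate or a non-parametric equivalent. It names no baseline covariate. The section presents itself as a summary and says that "A detailed analysis plan will be developed during the trial prior to commencement of analysis".

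The primary outcome is defined in two ways. The Primary outcome section gives a level: "The primary outcome will be the extravascular lung water index (EVLWI) measured by PiCCO thermodilution catheter at the end of the oesophagectomy". The abstract gives a change: "The primary outcome will be change in extravascular lung water index measured by PiCCO® transpulmonary thermodilution catheter at the end of the oesophagectomy".

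The Power and sample size estimate section works on the level. It uses a "mean post-operative EVLWI of 10.1 ml/kg and standard deviation of 2.9 ml/kg", a 20% difference, 80% power and a two-sided 0.05, and arrives at about 34 evaluable patients per arm. The pilot results in the same section are pre-to-post changes: +3.2 ml/kg in severe deficiency against +1.0 ml/kg otherwise, P = 0.013, from 50 patients. The article gives no pre-operative SD, no SD of change and no pre-post correlation. The outcome sections do not list a pre-operative EVLWI measurement, although a change cannot be computed without one.

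**The concern.** EVLWI before and after surgery in the same patient can be expected to correlate. When they do, a comparison of post-operative levels leaves explainable between-patient variation in the error term. A comparison of change scores removes some of it but subtracts the whole baseline value, and so adds noise when the correlation is modest. ANCOVA estimates how much of the baseline to subtract.

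Two things are at stake. The first is power. The trial is sized to just over 80%, and the article concedes that it has no direct data on the effect size, so extra precision at the same sample size is worth having. The second is chance imbalance. With 34 per arm, the arms can differ in pre-operative EVLWI by an amount that matters beside the target effect. A t-test on the level does not correct for this, and a t-test on change over-corrects.

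**Working it through.** **Inputs.** From the Power and sample size estimate section: post-operative mean 10.1 and SD 2.9 ml/kg; 20% difference; 34 per arm; two-sided alpha 0.05. Assumed, because the documents do not say: pre-operative SD also 2.9 ml/kg, and a pre-post correlation r, varied from 0.3 to 0.7.

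**Step 1: the plan's own figure.** Target difference = 0.20 × 10.1 = 2.02 ml/kg. The standard error of a difference in levels is 2.9 × √(2/34) = 0.703, so the noncentrality is 2.02/0.703 = 2.87. On the noncentral t distribution with 66 df, power is 80.8% at 34 per arm (79.6% at 33). The stated 34 is reproduced.

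**Step 2: SDs for the three analyses.**
- Level: 2.9, whatever r is.
- Change score: 2.9 × √(2(1 − r)).
- ANCOVA: residual SD 2.9 × √(1 − r²), with 65 df.

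**Step 3: power for 2.02 ml/kg at 34 per arm.**

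| Assumed r | SD, change | SD, ANCOVA | t-test on level | t-test on change | ANCOVA |
|---|---|---|---|---|---|
| 0.3 | 3.43 | 2.77 | 81% | 67% | 84% |
| 0.5 | 2.90 | 2.51 | 81% | 81% | 90% |
| 0.7 | 2.25 | 2.07 | 81% | 95% | 98% |

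The change-score test overtakes the level test only above r = 0.5, and below that it misses the planned 80%. ANCOVA is at least as powerful as both throughout. Even at r = 0.2 it has 82%, and at r = 0 it loses practically nothing (80.8%).

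**Step 4: chance imbalance.** With a pre-operative SD of 2.9, the standard error of the baseline difference between arms is again 0.70 ml/kg. At r = 0.5, an imbalance of one standard error shifts the level estimate by 0.5 × 0.70 = 0.35 ml/kg, and the change estimate by (1 − 0.5) × 0.70 = 0.35 ml/kg in the other direction. That is 0.35/2.02 = 17% of the target effect.

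**Step 5: can the pilot supply r?** Suppose that P = 0.013 came from a two-sample t-test on all 50 patients (48 df). Then t = 2.58, and the standard error of the 2.2 ml/kg difference in change is 2.2/2.58 = 0.853. The subgroup sizes are not given.
- A 25/25 split gives an SD of change of 0.853/√(1/25 + 1/25) = 3.01 and r = 1 − 3.01²/(2 × 2.9²) = 0.46. ANCOVA power is then 89%.
- A 10/40 split gives 2.41 and r = 0.65. ANCOVA power is then 96%.
- Letting the split run from 5/45 to 25/25 and the pre-operative SD from 2.0 to 3.3 ml/kg widens r to about 0.29 to 0.84, and power to 84% to over 99%.

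The pilot fits a useful correlation but does not fix one.

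**The case against.** **The case against.** The sentence on t-tests is generic and offered in brief, and a detailed plan that is not shown may specify adjustment. The t-test is valid under randomisation, matches the basis on which the trial was sized, and delivers the stated power. Chance imbalance does not invalidate it. On this view, preferring ANCOVA is a matter of taste.

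Most of this stands, and it limits the point to a recommendation. But the article does name a default, and that default is unadjusted. The detailed plan is the natural place to improve on it.

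**Stronger readings that the documents do not support.**
- *That the plan discards the baseline.* This is so only for the post-operative level. With "The primary outcome will be change in extravascular lung water index" as the definition, the t-test would be on the change and the baseline would be used.
- *That ANCOVA would raise power from 81% to 89–96%.* That range needs r of about 0.46 to 0.65, which rests on the unstated subgroup split, equal SDs and the form of the pilot test. If the pilot percentages refer to group means, they also fit the overall figures poorly: 3.2/0.27 + 3.2 = 15.1 and 1.0/0.10 + 1.0 = 11.0 ml/kg post-operatively, both above the stated 10.1. Moreover, 81% is the wrong comparator for a change outcome. At pilot SDs of change of 3.01 and 2.41, the change-score test has about 78% and 92.5%, so ANCOVA adds roughly 11 and 4 points.
- *That ANCOVA by itself settles the choice between parametric and rank tests.* Fixing the scale in advance does that, and it could be done for a t-test too.

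**A real reservation.** The Drug administration section places dosing seven days before surgery, so a pre-operative EVLWI may be measured after the dose. If treatment had already altered it, adjustment would remove part of the effect. The article's background locates the injury stimulus at one-lung ventilation, after that measurement, so the risk looks small. A change score carries it too.

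**Conclusion.** The point holds as an efficiency improvement. The planned t-test is not an error. Across assumed correlations of 0.3 to 0.7, adjusting for pre-operative EVLWI takes power from about 81% to between 84% and 98% if the outcome is the level. If the outcome is the change, the comparison is 67% to 95% for the t-test against the same 84% to 98%. The direction does not depend on the pilot inference. The size depends on r, which the documents do not give, and on equal pre- and post-operative SDs of 2.9 ml/kg. The gain also requires that a pre-operative EVLWI is recorded for each patient, which the abstract's definition implies but the outcome sections do not list.

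**What to change.** 1. Reconcile the abstract and the Primary outcome section on whether the outcome is the level or the change. With the pre-operative value as covariate, both give the same treatment estimate on a given scale, so the analysis need not wait on this, but the reported outcome should be unambiguous.
2. In the detailed analysis plan, make the primary analysis a linear model of post-operative EVLWI on treatment with pre-operative EVLWI as covariate. Fix the scale (untransformed or log) in advance, and report the adjusted difference with its 95% CI.
3. State when the pre-operative EVLWI is taken in relation to dosing, and keep the unadjusted comparison as a sensitivity analysis.
4. Adjust day-1 EVLWI in the same way. Do so for PaO2:FiO2 only if a pre-operative value is recorded.

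The cost is a few sentences before unblinding and, provided the pre-operative EVLWI is already collected, no new measurement. The small downside is the possibility that the baseline is post-dose, which the sensitivity analysis would help to show.

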## Abstract

**Background:**

Acute lung injury occurs in approximately 25% to 30% of subjects undergoing oesophagectomy. Experimental studies suggest that treatment with vitamin D may prevent the development of acute lung injury by decreasing inflammatory cytokine release, enhancing lung epithelial repair and protecting alveolar capillary barrier function.

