### Secondary outcomes

The trial secondary outcomes are clinical markers indicative of lung injury: PaO_2_:FiO_2_ ratio, oxygenation index, development of lung injury/ARDS during the first 28 days, ventilator and organ failure free days, survival (28 and 90 day) and safety and tolerability of vitamin D supplementation.

Lung injury will be defined by the American European Consensus Conference definition [35] as the acute onset of: (1) bilateral infiltrates on the chest x-ray; (2) hypoxaemia with a PaO_2_:FiO_2_ ratio of <40 kPa; and (3) absence of clinical evidence of left atrial hypertension. Ventilator free days are defined in accordance with the ARDSnet criteria as the number of calendar days after initiating unassisted breathing to day 28 after randomisation, assuming a patient survives for at least 48 consecutive hours after initiating unassisted breathing [36]. Un-assisted breathing is defined as one of at least 48 consecutive hours of: (1) being extubated with face mask, nasal prong oxygen, or room air; (2) T-tube breathing; and (3) tracheostomy mask breathing, CPAP = 5 cm H_2_0 without pressure support of intermittent mandatory ventilation assistance.

Organ failure free days are defined in a similar manner to ventilator free days with an organ failure free day being a day without evidence of non-respiratory organ failure. Organ failure will be defined as a sequential organ failure assessment (SOFA) score of greater than three [37].

Plasma indices of endothelial and alveolar epithelial function/injury, plasma inflammatory response will be measured by ELISA. Plasma vitamin D status (25(OH)D_3_, 1,25(OH)_2_D_3_, VDBP) and calcium will be assessed peri-operatively (pre-drug dose, pre-operative, post-operative, day 1 and day 3) as well as EVLWI day 1 post-operatively (measured at 9 am on day 1).

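### The protocol names logistic regression as its source of risk ratios, but the model gives odds ratios and no conversion step is stated (minor; secondary binary outcomes only)

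*Protocol article*

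**What the plan says.** Three statements in the Statistical analysis plan section of the protocol article bear on binary outcomes.

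- The basic comparison: "Chi-squared tests (or Fisher’s Exact tests) will be used for categorical variables".
- The scope of what follows: "For further examinations of relationships between a binary variable and known explanatory variables, the following tests will be applied as appropriate".
- The model and its effect measure: "Logistic regression will be used to provide the estimated risk ratios for the treatment effect", with a 95% confidence interval.

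Odds ratios are not mentioned anywhere in the article. The next sentence of the section pairs survival methods with hazard ratios, so the section does mean to fix a model and a measure together.

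Under Secondary outcomes, the outcomes listed include "development of lung injury/ARDS during the first 28 days, ventilator and organ failure free days, survival (28 and 90 day"). Of these, lung injury and survival at fixed times are binary. The only event rate for lung injury is in the Background paragraph of the abstract: "Acute lung injury occurs in approximately 25% to 30% of subjects undergoing oesophagectomy".

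The section also says: "A detailed analysis plan will be developed during the trial prior to commencement of analysis".

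**The concern.** A logistic model is linear in the log odds. Exponentiating its treatment coefficient gives the ratio of two odds, not of two risks. Risk ratios can be had from a logistic fit only through a further step, such as averaging predicted risks under each treatment and taking their ratio. The protocol states no such step.

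The distinction matters little when events are rare. It matters more when about one patient in four has the event, as the abstract suggests for ALI. If the software's default output were put in a table under the label of risk ratio, a benefit would look larger than it is, and so would a harm. A reader using that estimate to judge preventive effect or to plan a later trial would start from the wrong number.

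**Working it through.** **The protocol's own figure.** No sample size or effect is given for any binary outcome. The one stated calculation is for the continuous primary outcome, based on a "mean post-operative EVLWI of 10.1 ml/kg and standard deviation of 2.9 ml/kg". A 20% change is 0.20 × 10.1 = 2.02 ml/kg. With two-sided alpha 0.05, 80% power and equal arms:

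n per arm = 2 × (1.960 + 0.842)² × 2.9² / 2.02² ≈ 32.4, so 33 by the normal approximation. The t-based calculation gives 33.3, so 34. Adding six for dropout gives 40.

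This reproduces the stated 34 and 40 per arm. No binary outcome enters it, so the sample size does not depend on the sentence at issue.

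**Inputs for the check**

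- Control risk p0: 25% to 30%, from the abstract, with midpoint 27.5%. This is an approximate background rate, not a stated control-arm rate for the trial's own definition of lung injury to day 28.
- True risk ratio (RR): an assumption. The article gives no expected effect on ALI.

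**Formula.** With p1 = RR × p0,

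OR = [p1 / (1 − p1)] / [p0 / (1 − p0)] = RR × (1 − p0) / (1 − p1).

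If p1 is below p0, the last factor is below 1 and the OR is smaller than the RR. If p1 is above p0, the OR is larger. Either way the OR is further from 1. At RR = 1 the two agree.

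**Worked at p0 = 0.275**

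- Control odds: 0.275 / 0.725 = 0.3793.
- RR 0.50: p1 = 0.1375, odds 0.1375 / 0.8625 = 0.1594, OR = 0.1594 / 0.3793 = 0.42.
- RR 0.75: p1 = 0.20625, odds 0.20625 / 0.79375 = 0.2598, OR = 0.2598 / 0.3793 = 0.685, or 0.69.

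**Across the abstract's range**

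| Assumed RR | OR at p0 = 0.25 | OR at p0 = 0.275 | OR at p0 = 0.30 |
|---|---|---|---|
| 0.50 | 0.43 | 0.42 | 0.41 |
| 0.75 | 0.69 | 0.69 | 0.68 |
| 0.80 | 0.75 | 0.74 | 0.74 |
| 1.50 | 1.80 | 1.85 | 1.91 |

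Read as a risk ratio, the OR would turn a true 50% relative reduction into 57% to 59%, and a true 20% reduction into 25% to 26%.

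**Rarer events, for contrast.** A true RR of 0.50 corresponds to an OR of 0.495 at 2% control risk, 0.487 at 5% and 0.474 at 10%. For a rare outcome the mislabelling would be almost harmless. The article gives no expected rates for 28- or 90-day survival in this trial, so the size there cannot be stated.

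**The shift beside sampling error.** Take 5 events of 40 against 10 of 40, an invented but plausible result.

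- RR = 0.50; SE of log RR = √(1/5 − 1/40 + 1/10 − 1/40) = 0.50; 95% CI 0.19 to 1.33.
- OR = (5/35) / (10/30) = 0.43; SE of log OR = √(1/5 + 1/35 + 1/10 + 1/30) = 0.60; 95% CI 0.13 to 1.39.

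The point estimate moves by 0.07, and both intervals are wide and include 1.

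**Limit of the arithmetic.** The formula is for an unadjusted model, while the sentence concerns models with explanatory variables. An adjusted odds ratio is not collapsible and generally lies further from 1 than the crude one, so the figures are illustrative.

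**The case against.** The strongest reply is that the sentence does not say exponentiated coefficients will be presented as risk ratios. It says the model will be used to provide risk ratios, and standardising a logistic fit does exactly that. On that reading nothing is overstated. Nor is anything overstated if the trial team simply reports odds ratios under their right name. This stands: the overstatement is conditional on an odds ratio being labelled or read as a risk ratio.

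A second reply is that the model is a secondary tool. It is introduced for further examination of binary variables, to be used as appropriate, and the stated comparison for categorical outcomes is chi-squared or Fisher's exact. This also stands.

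A third is that the passage is a brief summary and a detailed plan is to follow. This stands only in part. The later plan may well put it right, but the point is about something the article states, not something it leaves out. A plan that copied the sentence would carry the mismatch forward.

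A reader might go further and infer that the trial will overstate vitamin D's effect on ALI, and so distort its main preventive claim and any later meta-analysis. The document does not support that. ALI is listed among the secondary outcomes without being ranked above the others, the primary outcome is continuous EVLWI, and the Discussion presents the trial as a proof of concept based on biomarkers. A meta-analyst with the event counts can compute the risk ratio directly.

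**Conclusion.** The mismatch is real but minor. As written, the protocol assigns risk ratios to a model whose coefficients give odds ratios and does not say how one becomes the other. If the odds ratio were published as a risk ratio for an outcome as common as ALI, the apparent relative reduction would be too large by about 5 to 9 percentage points, for assumed true risk ratios between 0.50 and 0.80 at control risks of 25% to 30%. The direction, further from 1 for benefit or harm, does not depend on those assumptions. The size does, because the event rate is only approximate and the effects are assumed.

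The point reaches only the further regression analyses of secondary binary outcomes. It leaves untouched the primary EVLWI analysis, the sample size and the chi-squared or Fisher tests. The null values of the two measures also coincide.

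**What to change.** Amend the one sentence in the Statistical analysis plan section, and carry the change into the detailed plan, in either of two ways:

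- state that logistic regression will give odds ratios with 95% confidence intervals, and label them so in every table; or
- if risk ratios are the intended measure, name the method that will estimate them with 95% confidence intervals: standardisation from the fitted logistic model, log-binomial regression, or Poisson regression with robust standard errors.

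Either resolves the point in full. The cost is a line of text and, for the second option, a different model call or a post-estimation step. No extra data, patients or change to trial conduct is needed.
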